# 1. RATIONALE AND BACKGROUND

Resistance to commonly used antimalarial drugs represents the major drawback and obstacle for controlling malaria in endemic countries. Currently, the geographic distribution of *P. falciparum* resistance to chloroquine (CQ) almost corresponds to that of the parasite itself and it is severe in many countries. Several countries have changed their first line treatment from CQ to other regimens, usually sulfadoxine-pyrimethamine (SP), but resistance to the latter has rapidly reached critical levels in some areas of East and Central Africa and a public health disaster might be imminent. Unfortunately, only few available alternative drugs are ready for deployment. It is generally agreed that endemic countries should opt for combination treatment, i.e. the association of 2 or more antimalarial drugs with different metabolic targets. Artemisinin derivatives (AS) and consequently artemisinin-containing combinations (ACT) have several advantages as they produce a rapid clinical and parasitological cure, reduce gametocyte carriage rate and are generally well tolerated. In Africa, studies on ACT (artesunate with either CQ, amodiaquine (AQ) or SP) have been carried out in a few thousands children with uncomplicated malaria. Good safety and efficacy were reported when the partner drug was also efficacious. However, at least 2 of the 3 drugs mentioned above (CQ and SP) can no longer be considered as useful partner drugs for combination with AS because of their confirmed low efficacy. Several African countries have already opted for ACT (for example: Burundi for AQ+AS, Zanzibar for AQ+AS and artemether + lumefantrine (AL), Zambia for AL; Kenya, Rwanda, Uganda and Tanzania might or are about to change to AL), but additional information for their optimal deployment is still required. Besides a non-co-formulated AQ+AS, the only other possible alternative is AL, which is moderately expensive and has a complex dosage. The need to provide African Ministries of Health with reliable information on ACT safety, efficacy and effectiveness (NB, the latter is not addressed in this proposal) is obvious. We therefore propose to test 4 combinations, namely amodiaquine + artesunate (AQ+AS), dihydroartemisinin + piperaquine (DHAPQ), artemether + lumefantrine (AL) and chlorproguanil-dapsone + artesunate (CDA), the first 3 being co-formulated. The studies will be carried out in 7 African countries covering a variety of epidemiological situations. All partners involved are experienced in the conduct of clinical trials and most of them have been working in this field for several years. Moreover, the close relationship of institutions such as the EANMAT to the countries' Ministries of Health is a guarantee for the rapid uptake of the project's results for the review and modification of their national antimalarial drug policy.

## 1.1 Drugs to be tested

### Chlorproguanil–dapsone + artesunate (CDA)

Chlorproguanil–dapsone (CD) is a fixed-dose antifolate combination that has been developed jointly by GlaxoSmithKline and WHO/TDR (Tropical Disease Research). CD received approval from the UK Regulatory Agency in July 2003 for the treatment of uncomplicated falciparum malaria in non-pregnant adults and children and has recently become available in several countries in Africa. Unlike sulfadoxine-pyrimethamine (SP), CD is rapidly eliminated from the body (approximate half-lives of chlorproguanil and dapsone are 24h and 12h), resulting in low selection pressure for drug resistance. Data from the Phase III clinical programme conducted in children in sub-Saharan Africa demonstrated that CD achieved significantly higher cure rates compared to SP (96% vs 89%;  $p < 0.001$ ) and was well

tolerated. Importantly, SP-resistant infections acquired in Africa have been responsive to CD treatment. In contrast to pyrimethamine, chlorproguanil retains therapeutic activity against parasites with the common *dhfr* mutation conferring resistance against pyrimethamine: ser-108-asn, asn-51-ile and cys-59-arg.

CD is well tolerated in young children and most of the serious adverse events recorded are more likely to be disease-related than drug-related. One percent of patients taking CD and 1% of those taking SP reported serious adverse events, most commonly red blood cell disorders. Dapsone is known to cause methaemoglobinaemia and haemolysis (especially in G6PD deficient people). Clinically significant increases in methaemoglobin were not seen in SP-treated patients, but were observed in 4.2% of those given CD (all mild cases and 1 moderate case, all of limited duration). None of the children showed dyspnoea, the main symptom of high methaemoglobinaemia, and no action was required by attending physicians. Severe hemolysis is of concern because it is a feature of falciparum malaria, making it difficult to identify cases of drug-induced haemolysis. G6PD-deficient children in the CD group were more likely than similar patients in the SP group to have a > 2g/dL haemoglobin drop when compared to those without G6PD deficiency, but by day 14 Hb values in both groups had been restored to baseline. Larger haemoglobin falls after treatment with CD than after SP have been reported previously. Other genetic polymorphisms, such as those in candidate genes responsible for metabolism of CD, are also potential determinants of the risk of adverse events.

Although Lapdap exerts a significantly lower selective pressure than SP (Nzila et al, 2000), and it is currently highly effective, activity will be greatly reduced by the selection of one further DHFR mutation. This mutation, at codon 164 was selected by SP use in both South America and South-East Asia, and has been found at low frequency in Tanzania. The use of CD as monotherapy may therefore increase selective pressure for the 'quadruple DHFR mutant'. Associating CD with artesunate can considerably increase its antimalarial activity and at the same time might delay the selection of the quadruple DHFR mutants. A trial investigating the safety and efficacy of non co-formulated CD and artesunate in children 6-59 months old with uncomplicated malaria is ongoing in Rwanda. Preliminary results show a relatively good efficacy and no major safety problem.

### **Artemether –lumefantrine (AL)**

This is a fixed-dose combination of artemether (a semi-synthetic artemisinin derivative) and lumefantrine (a slowly eliminated drug also referred to as benflumetol). The registered indications and branding for AL cover treatment of uncomplicated malaria caused by mono or mixed *Plasmodium* infections. The combination is expected to confer mutual protection against resistance and prevent recrudescence after artemether therapy. The components of this combination were originally studied and developed in China by the Academy of Military Medical Sciences (AMMS), Beijing and Kunming Pharmaceutical Factory (KPF), Kunming. The fixed combination has been registered in China since 1992 and has undergone further development when Novartis signed a collaborative agreement in 1994 with AMMS, KPF and CITITEC, the technology arm of the China International Trust and Investment Corporation (CITIC). Studies for the international registration started in 1995. AL was registered in Switzerland in 1999 and has since received marketing authorisation in several endemic and non-endemic countries. Recently, an agreement was reached between Novartis and WHO for AL to be made available to the public sector of developing countries at a preferential price. Few clinical trials, mostly with the four-dose regimen, have been conducted both with the

original Chinese combination product and the subsequent product used for international registration. A Cochrane review has, in 2003, identified eight randomized, controlled trials comparing AL with standard treatment for uncomplicated falciparum malaria (2117 participants). From the meta-analysis, it was concluded that the four-dose AL regimen was superior to CQ and equivalent to SP in areas of CQ resistance but inferior to mefloquine and mefloquine-artesunate in areas of multidrug resistance. The six-dose regimen was also equivalent to mefloquine-artesunate but was better tolerated. A collaborative project between Novartis and WHO has led to a more user-friendly packaging of the six-dose treatment, which is now being field tested. A paediatric formulation is also being developed and trials have been conducted for regulatory submission to extend the label to cover children who weigh less than 10 kg.

### **Artesunate-amodiaquine (AQAS)**

Several clinical trials involving AQAS have been completed in Africa. Two trial in Rwanda comparing non-coformulated AQAS with either AQ+SP and with DHAPQ showed that the former is a well tolerated combination with an efficacy at day 28 after treatment above 90%. A blister pack of AQAS has been developed and several African countries have chosen AQAS as first line treatment. AQAS has now been developed as fixed-dose combination and is undergoing registration after the relevant pre-clinical and clinical studies.

### **Dihydroartemisinin-piperaquine (DHAPQ)**

DHAPQ was developed in China and is registered in China and Cambodia. Non GMP DHAPQ has been evaluated extensively in clinical trials in Thailand, Vietnam, Cambodia and China, efficacy has been high and tolerability uniformly good in all trials in multidrug-resistant areas, where piperaquine-resistance was common after its extensive use for mass prophylaxis. In Africa, DHAPQ has been evaluated in Rwanda in children 6-59 months old with uncomplicated malaria. The treatment was highly efficacious (95% adequate clinical and parasitological response at day 28 after treatment) and well tolerated. Initially, the co-formulation included primaquine and trimethoprim (CV8), which is still part of national policy in Vietnam. Piperaquine is an orally active bisquinoline discovered by Rhône-Poulenc in the early 1960s and developed for clinical use in China in 1973. Piperaquine is approximately equivalent to chloroquine against sensitive parasites, but is significantly more effective than chloroquine against resistant *P. falciparum*. Piperaquine replaced chloroquine as the recommended treatment for falciparum malaria in China in 1978. Overall, 194 140 kg of piperaquine phosphate, equivalent to 140 000 000 adult doses, were used for mass prophylaxis and treatment. Surveillance at the time found no adverse events other than rare cases of a rash. However, reports about emerging parasite resistance to piperaquine from southern China, an area of intensive use of piperaquine, are of concern. Dihydroartemisinin is the active metabolite of artesunate and artemether. It has equivalent clinical efficacy to the more widely used artesunate. A development programme has been agreed between Holleykin Pharmaceuticals and Guangzhou University (China), The University of Oxford, MMV, and Sigma-Tau Industrie Farmaceutiche Riunite SpA to support the international registration of the drug. A multi-centre phase III clinical trial comparing DHAPQ with AL in Africa and with mefloquine+artesunate in Asia is ongoing.

## 2. TRIAL OBJECTIVES AND PURPOSE

The main objective is to compare the safety and efficacy of 4 artemisinin-based combination therapies (ACT), i.e. amodiaquine-artesunate (AQ+AS), artemether-lumefantrine (AL), dihydroartemisinin-piperaquine (DHAPQ), chlorproguanil-dapsone-artesunate (CDA), for single and repeat treatments of uncomplicated malaria in African children. Safety will be determined by registering adverse events and grading, laboratory, and vital signs evaluations. Their incidence will be compared between the different study arms.

Specific objectives are the following:

1. To evaluate the efficacy of the 4 ACTs for the treatment of children with uncomplicated *P. falciparum* malaria (first active follow-up);
2. To determine after the first active follow-up the incidence rate of a second clinical episode of uncomplicated *P. falciparum* malaria;
3. To evaluate the efficacy of treating the second clinical episode of uncomplicated *P. falciparum* malaria with the same ACT used for the first one (second active follow-up);
4. To evaluate during the active and passive follow up the safety of the 4 ACTs for the treatment of children with uncomplicated *P. falciparum* malaria;
5. To establish the impact of using CDA on the selection of *P. falciparum* genotypes linked to SP resistance.

## 3. TRIAL DESIGN

### 3.1 Study Design

This is a multi- centre, randomized, open label, multi-armed study involving 10 investigational centres that will enrol 5100 patients, 510 per site, 170 per arm. The 4 combinations will be tested and compared in different countries, with different malaria transmission and resistance characteristics (Table 1). A three-arm trial maximises the amount of information collected and, at the same time, keeps the individual studies manageable.

The total number of patients treated by each study treatment will be between 1700 (DHAPQ) and 1020 (AQ+AS and CDA). For the comparisons between treatment arms, the highest number of patients per arm will be 1360 (DHAPQ vs AL), and the lowest 340 for the comparison between AQ+AS and CDA. This is slightly different from what had been planned in the proposal submitted to the EDCTP. The Rwandan collaborators have requested not to test AQ+AS on the ground that this combination will not be used as first or second line treatment. Indeed, resistance to AQ in Rwanda is already substantial, particularly in the site of Rukara. This is why the arm AQ+AS has been replaced by DHAPQ.

The main justification for not performing a double-blind study is the requirement to use the double-dummy technique requiring placebos for 3 arms drugs per site, resulting into a treatment schedule which would be very laborious for the patient. In order to ensure concealment of treatment allocation and avoid other biases, the following requirements will be assured:

- 1 The randomization list will be generated prior the beginning of the study. Treatment allocation will be concealed until the completion of the screening and the final recruitment of the patient (see section 3.10);
- 2 The interpretation of the PCR reading will be blinded/masked with regard to the treatment allocation of the patients (see section 3.9);
- 3 An independent Data Monitoring Board will review all efficacy and safety data (see section 13.2).

**Table 1. Study treatment to be tested by country.**

| Country      | Sites     | Transmission (EIR)         | CQR % | SPR%          | Study treatments |       |       |
|--------------|-----------|----------------------------|-------|---------------|------------------|-------|-------|
| Burkina Faso | Nanoro    | Seasonal high (50-60)      | 66    | 27            | AQ+AS            | DHAPQ | AL    |
| Nigeria      | Calabar   | Perennial high             | 45    | 30            | AQ+AS            | DHAPQ | AL    |
| Zambia       | Ndola     | Seasonal mesoendemic       | High  | >20 in adults | AQ+AS            | DHAPQ | AL    |
| Gabon        | Lambarené | Perennial high (50)        | 100   | 21            | AQ+AS            | DHAPQ | AL    |
| Uganda       | Mbarara   | Mesoendemic                | 81    | 61            | AQ+AS            | CDA   | DHAPQ |
| Uganda       | Jinja     | Seasonal low (6)           | 28    | 49 (CQ+SP)    | DHAPQ            | CDA   | AL    |
| Uganda       | Tororo    | Seasonal high (>70)        | 45    | 9-15          | DHAPQ            | CDA   | AL    |
| Rwanda       | Rukara    | Seasonal high              | 40    | 35 (CQ+SP)    | DHAPQ            | CDA   | AL    |
| Rwanda       | Mashesha  | Seasonal high              | 50    | 12            | DHAPQ            | CDA   | AL    |
| Mozambique   | Manhiça   | Perennial mesoendemic (15) | 78    | 22            | AQ+AS            | CDA   | DHAPQ |

EIR: Entomological Inoculation rate; CQR: Chloroquine resistance; SPR: sulfadoxine-pyrimethamine resistance; AQ+AS: amodiaquine-artesunate; DHAPQ: dihydroartemisinin-piperaquine; AL: artemether-lumefantrine; CDA : chlorproguanil-dapsone-artesunate;

### 3.2 Primary Endpoint

There will be several primary end points:

1. PCR unadjusted treatment failure up to day 28 (TF28U): all treatment failures detected during the first active follow up, regardless of genotyping.
2. PCR adjusted treatment failure up to day 28 (TF28A): all early failures before day 14 plus the recurrent parasitaemias detected at day 14 or later and classified by genotyping as recrudescence.

The TF is defined according to the WHO criteria (WHO 2003) as the sum of early\* and late\*\* treatment failures.

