#### \* Early Treatment Failure (ETF) (one of the following)

- (i) Development of danger signs or severe malaria (see Appendix V) on Day 0, Day 1, Day 2 or Day 3, in the presence of parasitaemia,
- (ii) Parasite density on Day 2 > Day 0 count, irrespective of axillary temperature,

- (iii) Presence of parasitaemia on Day 3 with fever (axillary temperature  $\geq 37.5^{\circ}\text{C}$ ),
- (iv) Parasitaemia on Day 3  $\geq 25\%$  of count on Day 0.

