#### Late Clinical Failure (LCF):

- (i) Development of danger signs or severe malaria after Day 3 in the presence of parasitaemia, (See Appendix V for the criteria of severe malaria/danger signs).
- (ii) Presence of parasitaemia and fever on any day from Day 4 to Day 28, without having previously meet the criteria of ETF.

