#### Late Parasitological Failure (LPF):

Reappearance of parasitaemia after day 3 in the absence of fever (axillary temperature  $<37.5^{\circ}\text{C}$ ) without having previously meet the criteria of ETF or LCF.

The adequate clinical and parasitological response (ACPR) is 1-TF (28 or 63, unadjusted or adjusted). It is defined as absence of parasitaemia at the end of the follow up period (day 28-63), irrespective of axillary temperature without previously meeting any of the criteria of early and late treatment failure. In the adjusted estimates, patients with late asexual parasite reappearance (with or without fever) will be considered ACPR if the PCR analysis shows a new infection rather than a recrudescence.

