### **3.3 Secondary Endpoints**

The secondary endpoints will be:

- PCR unadjusted treatment failure up to day 63 (TF63U): TF28U plus all recurrent parasitaemias (symptomatic or asymptomatic) detected between day 29 and day 63 by passive follow up, regardless of genotyping.
- PCR adjusted treatment failure for the whole period of passive surveillance (TFAPS): TF28A plus all episodes of recurrent parasitaemia identified as recrudescence by genotyping.
- Fever clearance time (FCT): Fever clearance time will be defined as the time (in days) from the time of randomization to the first two consecutive measurements on 2 different days of axillary temperature below  $37.5^{\circ}\text{C}$ .
- Asexual parasite clearance time (PCT): Asexual parasite clearance time will be defined as the time (in days) from time of randomization to 2 consecutive negative blood slides (collected at different days). The time to the event will be taken as the time to the first negative slide.
- Gametocytaemia (prevalence and density) at day 7, 14, 21 and 28 after treatment (for both active follow-ups);

- Hb changes day 3, 7, 14 and 28 (first and second follow up);
- Clinical malaria after first active follow-up;
- Clinical malaria after second active follow-up;
- TF second clinical episode (D28 and D63);
- DHFR mutations at day 0 first follow-up and day re-appearance of parasitaemia (for patients treated with CDA).
- Safety profiles: Subjects will be monitored for 28 days (first and second follow up) for possible development of adverse events. All adverse events will be recorded on the specific form in the CRF. Vital signs, blood chemistry and haematology will be monitored and changes in relevant laboratory parameters will be assessed.

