6 PCR

A blood sample will be collected on filter paper (Whatmann 3MM) at day 0 before treatment and on day 1 and, from day 14 onwards, every time a blood slide is done. Samples from patients classified as late treatment failure will be subsequently used for parasite genotyping. An additional blood sample at day 0 will be collected for later determination of the G6PD status. The collection will be carried out only in sites where CDA is tested.

7 Laboratory Tests

Blood haemoglobin, red blood cell count, total white blood cell count, differential count.

Total bilirubin, ALAT and creatinine will be measured.

8 Administration of the Study Drugs

9 Adverse Events Report

All adverse events will be recorded. See section 7.1.4 for the details on the information collected.

10 Concomitant Medications

Any medications taken by the study subject will be recorded in the CRF.

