### **Unscheduled visits throughout follow up**

During this visits, the same procedures as day 21 will be applied. Hb will be measured if the patient is classified as treatment failure.

The PCR readings will be centralised and masked to the treatment allocation of study subjects, i.e. by personnel different from the treating physician/investigator. In addition, a centralized and independent double-check of a significant percentage of blood slides and filter paper blood samples (PCR) will be carried-out. The percentages of slides and films to be reviewed and the corresponding statistical justifications will be specified in the Statistical Analysis Plan.

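### TF28A is worded inconsistently for recurrences on days 4 to 13, and the scheduled day-7 visit takes no filter paper

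*Protocol*

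**What the plan says.** **Endpoint rule.** Protocol section 3.2, and the Synopsis in the same terms, define TF28A as "all early failures before day 14 plus the recurrent parasitaemias detected at day 14 or later and classified by genotyping as recrudescence". Section 3.2 then defines treatment failure "as the sum of early\* and late\*\* treatment failures", with a definition under each term.

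**Early failure.** None of the early-failure criteria looks beyond day 3. The danger-sign criterion, for example, applies on "Day 0, Day 1, Day 2 or Day 3, in the presence of parasitaemia".

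**Late failure.** Late clinical failure is "Presence of parasitaemia and fever on any day from Day 4 to Day 28". Late parasitological failure likewise starts after day 3.

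**PCR rule for late reappearance.** For the PCR-adjusted endpoints the rule is: "patients with late asexual parasite reappearance (with or without fever) will be considered ACPR if the PCR analysis shows a new infection". No starting day is given.

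**Sampling and genotyping.** Section 3.10.1 (Day 0, PCR item) collects filter paper on days 0 and 1 and then "from day 14 onwards, every time a blood slide is done. Samples from patients classified as late treatment failure will be subsequently used" for genotyping. The text for days 7, 14 and 21 also starts filter paper at day 14. In the follow-up chart (Synopsis and Figure 1 in section 3.8), day 7 has a blood film but no filter paper.

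**Unscheduled visits.** The chart marks filter paper for spontaneous attendance on any other day, and section 3.10.1 says "During this visits, the same procedures as day 21 will be applied".

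**DHFR endpoint.** Section 3.3 lists "DHFR mutations at day 0 first follow-up and day re-appearance of parasitaemia (for patients treated with CDA").

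**The concern.** The word for early failure carries two meanings within one section: before day 14 in the TF28A rule, and days 0 to 3 in the definition beneath it. A child first parasitaemic again on day 9 is a failure without genotyping under the first, and a late failure under the second. The PCR sentence would then reclassify that child as an adequate response if the strain is new.

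TF28A is one of two primary endpoints, and the secondary endpoint for the whole passive surveillance period is built on it. If the PCR sentence is followed as written, the result for a day 4 to 13 recurrence depends on whether a blood spot exists. That depends in turn on whether the visit was scheduled and on which sampling passage the site followed. The trial is open label, so a primary-endpoint rule should not be left for the analyst to choose.

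The sampling gap is separate. An analysis plan can choose between two definitions, but it cannot recover a day-7 blood spot that was never taken.

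**Working it through.** The point is mainly textual. The steps follow a recurrence first seen on days 4 to 13 through the protocol.

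1. **By the day limit in the TF28A rule (section 3.2).** It falls before day 14, so it counts as a failure without genotyping.
2. **By the late-failure definitions and the PCR sentence (section 3.2).** It is a late failure, and becomes an adequate response if PCR shows a new infection. The genotyping sentence in section 3.10.1 agrees, because it covers late failures without a day limit.
3. **Whether a sample exists.**

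| Where the recurrence is found | Blood film | Filter paper |
|---|---|---|
| Scheduled day 7 | Yes | No: the chart and both text passages agree |
| Unscheduled, days 4 to 13 | Yes | Yes by the chart and the unscheduled-visit text; no by the Day 0 PCR item |
| Day 14 or later | Yes | Yes |

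4. **Whether a later visit could supply it.** Section 4.4 stops active follow-up at failure and gives rescue treatment, so no later active-follow-up visit samples that recurrence. The indeterminate category in section 3.4 covers failed amplification and does not name a sample that was not taken.
5. **DHFR.** For a CDA patient found positive at the day-7 visit, the sample that section 3.3 needs for the day of reappearance is not planned.

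**Size.** Let b be the share of an arm with other TF28A failures, q the share first recurring on days 4 to 13, and r the recrudescent share of those. None of these is in the documents.

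- Failure whatever the PCR result: TF28A = b + q.
- PCR decides: TF28A = b + qr.
- Difference: q − qr = q(1−r).

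With an assumed b = 5%:

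| q | r | Regardless of PCR | By PCR | Difference |
|---|---|---|---|---|
| 0.5% | 0.5 | 5.5% | 5.25% | 0.25 points |
| 3% | 0.5 | 8.0% | 6.5% | 1.5 points |
| 3% | 0.8 | 8.0% | 7.4% | 0.6 points |
| 3% | 1.0 | 8.0% | 8.0% | 0 |

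At q = 3% and r = 0.5, this is 170 × 0.03 × 0.5 = 2.55 children per arm and site. It is an upper bound for those inputs: if day-7 recurrences without a sample stay failures, only the sampled ones can be reclassified. The shift in a between-arm difference is q₁(1−r₁) − q₂(1−r₂). It vanishes if the arms are alike and cannot exceed the larger single-arm shift.

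**Scale.** Section 3.5 gives a 10-point margin per site and a detectable difference of 4 to 6 points pooled. Its 155 per arm reproduces with 90% efficacy in both arms, one-sided 5% and 90% power: (1.645 + 1.282)² × 2 × 0.9 × 0.1 / 0.10² = 154.2, rounded up to 155. That number is not in dispute here.

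**The case against.** The strongest reply is that the intention is clear. The TF28A rule splits follow-up into two complementary parts at day 14, and scheduled filter paper restarts on that day. No paper is planned at day 7 because failures before day 14 need no genotyping. The PCR sentence takes effect only where a PCR result exists, so it has no force at the one scheduled visit between days 4 and 13. For unscheduled visits, the day-21 procedures could be read as carrying over the same day-14 start. Most of this stands: counting all failures before day 14 is the likely intention. It does not remove the conflict, because neither the PCR sentence nor the genotyping sentence has a day limit, and the chart's mark for any other day plainly collects paper earlier.

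Four stronger readings are tempting but not supported:

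- A reader might infer a third classification, in which a day 4 to 13 recurrence falls into neither part of TF28A and counts as an adjusted success without genotyping. That would leave the day-14 limit on early failures with no function, and no passage says it.
- A reader might set that third reading against the first and assume recurrence rates that give a shift of up to 5 points. The documents give no such rates.
- A reader might infer that early DHFR samples are lost in general. The loss is certain only at the scheduled day-7 visit, since the chart and the unscheduled-visit text provide paper at other times.
- A reader might argue from the 24-hour chlorproguanil half-life in section 1.1 that samples from day 14 are uninformative because little drug remains. The endpoint compares mutations at day 0 with those at reappearance, and a day-14 recrudescence still descends from parasites that survived treatment.

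**Conclusion.** The point holds in this form: the wording of TF28A conflicts with the protocol's own failure definitions, its PCR sentence and its genotyping sentence for recurrences on days 4 to 13. The sampling passages also disagree for unscheduled visits in that window. At the scheduled day-7 visit a recurrence cannot be genotyped and, in a CDA patient, has no DHFR sample.

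The effect on TF28A cannot be derived from the documents. The plausible contrast is at most q(1−r) in an arm: 1.5 points at an assumed q = 3% and r = 0.5, less for smaller q or larger r. That is well inside the 10-point site margin, and smaller than the 4 to 6 points pooled but not trivial beside them. Early recurrence could differ by arm, since section 1.1 describes chlorproguanil-dapsone as rapidly and lumefantrine as slowly eliminated, but the protocol does not quantify this. TF28U does not depend on genotyping and is unaffected.

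The case for correction rests on having a single rule for a primary endpoint and on a sample that cannot be recovered later, rather than on a large expected bias.

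**What to change.** 1. In the Synopsis and section 3.2, replace the first part of the TF28A rule with: all treatment failures, early or late, before day 14, regardless of genotype.
2. Limit the sentence that turns a PCR-confirmed new infection into an adequate response, and the genotyping sentence in section 3.10.1 as it applies to TF28A, to recurrences from day 14 onwards.
3. Align both follow-up charts with the section 3.10.1 texts for Day 0 (PCR item), days 7, 14 and 21, and unscheduled visits, so that a filter paper is taken with any positive slide from day 4, the scheduled day 7 included.
4. Use the added samples for the DHFR endpoint and for a sensitivity analysis of TF28A that classifies recurrences on days 4 to 13 by PCR. They do not change the primary rule.

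The cost is a few sentences, a chart footnote, and a blood spot from a finger prick already made for the slide in the few children positive on those days.
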